## Abstract

**Background:**

Chronic shoulder pain (CSP) is the third most common type of musculoskeletal pain. It has a major impact on health-related quality of life. In Chinese medicine, CSP is considered one of the conditions most amenable to treatment with acupuncture. The purpose of this study is to evaluate the efficacy of local acupoints in combination with distal acupoints in pain relief and shoulder function improvement in CSP patients.

**Methods/Design:**

This is a multicenter, single blind, factorial randomized controlled clinical trial. A total of 164 participants will be randomly allocated to four different groups: Group A will receive acupuncture at local acupoints in combination with distal acupoint. Group B will receive acupuncture at local acupoints in combination with distal non-acupoint. Group C will receive acupuncture at local non-acupoints in combination with distal acupoint. Group D will receive acupuncture at local non-acupoints in combination with distal non-acupoint. Each group will receive 12 treatments of acupuncture one to three times per week for six weeks in total. The primary outcome is shoulder pain intensity, which is graded using a 100 -mm Visual Analogue Scale. The assessment is at baseline (before treatment initiation), 6 weeks after the first acupuncture, 10 weeks after the first acupuncture and 18 weeks after the first acupuncture.

**Discussion:**

This trial will be helpful in identifying whether acupuncture at local acupoints in combination with distal acupoints may be more effective than needling points separately.

**Trial registration:**

International Standard Randomized Controlled Trial Number Register: ISRCTN61861069 (http://www.controlled-trials.com).

## Background

Chronic shoulder pain (CSP) is the third most common type of musculoskeletal pain. It has a major impact on health-related quality of life [1]. Disorders of the shoulder muscles and tendons (rotator cuff) are thought to be the most common causes of the pain [2]. The true prevalence is unknown, varying in different reports from 4 to 34% [3]. The conventional treatments for shoulder pain are NSAIDs, physiotherapy, cortisone injections and ‘wait and see’ [4,5]. Unfortunately, none of these treatments are clearly proven to be effective for CSP in the long run [4-6]. In Chinese medicine, CSP is considered one of the conditions most amenable to treatment with acupuncture [4]. The purpose of this study is to evaluate whether local acupoints in combination with distal acupoints are more effective than local acupoints or distal acupoints alone in pain relief and shoulder function improvement in CSP patients.

## Methods/Design

### Ethics

The study is in accordance with the Declaration of Helsinki and has been approved by the Research Ethical Committee of Beijing Hospital of Traditional Chinese Medicine Affiliated to Capital Medical University(reference: 201315). This trial was registered with ISRCTN at Current Controlled Trials (ISRCTN61861069). Before randomization all patients will be requested to sign a written informed consent, and they will also be given enough time to decide whether they are willing to participate in the trial or choose other treatment options.

### Population

Patients will be recruited in acupuncture clinics in the Beijing Hospital of Traditional Chinese Medicine Affiliated to Capital Medical University, the Beijing Huairou District Hospital of Traditional Chinese Medicine, and the Dongzhimen Hospital Affiliated to Beijing University of Chinese Medicine, with a target sample size of 164 subjects. The trial will be executed from January 2014 to December 2015.

### Recruitment of participants

Two strategies will be used to recruit participants with CSP. One is to recruit participants in outpatient clinics from the three hospitals mentioned above. The other is to show recruitment posters outside the clinics. The posters will contain brief introductions about the population needed, the free acupuncture treatments offered to eligible participants, and the contact information of the researcher. Screening forms will be completed by interested patients, which will be conducted via a face-to-face interview and assessment with a researcher at one of the hospital sites prior to randomization.

### Inclusion criteria

Patients who meet all of the following conditions will be considered for enrollment. The inclusion criteria are as follows: aged between 25 and 65 years (either sex); present with a primary complaint of shoulder pain with one-sided shoulder pain for at least six weeks and up to two years; a pain score of 50 mm or more on a 100 -mm visual analogue scale (VAS); plain radiography is normal, but osteoporosis or a calcification shadow may be present; individuals had not received acupuncture in the preceding month; and a signed informed consent form.

### Exclusion criteria

The exclusion criteria are as follows: referred pain from the cervical spine, history of shoulder trauma, shoulder surgery, stoke, ipsilateral breast surgery, heart diseases and severe hypertension; osteoarthritis of the glenohumeral joint or systemic bone and joint disorder (rheumatoid arthritis); endocrine diseases such as hyperthyroidism; severe infection; and undergoing current therapy involving analgesics.

### Interventions

The participating acupuncturists will be members who have been qualified for at least three years and who hold a Chinese medicine practitioner license from the Ministry of Health of the People’s Republic of China. The acupuncture treatments will be performed according to a treatment protocol already developed for this purpose. This will allow for each patient having a customized treatment within a standardized theory-driven framework. All patients will have a standardized interview and receive more information about the study and treatments. Patients are informed in a manner suggesting that four different types of acupuncture treatment are compared some are traditional and others are new. As the effect of all four is uncertain, terms such as ‘placebo’ or ‘sham’ were not used. Similar strategies of informed consent have been used in most previous acupuncture trials [7]. After obtaining informed consent from each participant and completing a baseline evaluation, they will receive 12 treatments of acupuncture, one to three times per week for six weeks in total. Time points are as shown in Figure 1.

**Figure 1 F1:**
[figure not shown]
Flow chart.

Patients who meet the inclusion criteria are randomized to one of four treatment groups:

Group A will receive acupuncture at local acupoints in combination with distal acupoint.

Group B will receive acupuncture at local acupoints in combination with distal non-acupoint.

Group C will receive acupuncture at local non-acupoints in combination with distal acupoint.

Group D will receive acupuncture at local non-acupoints in combination with distal non-acupoint.

We selected local acupoints and local non-acupoints on the same side of the shoulder lesion, while distal acupoint and distal non-acupoint were opposite to the shoulder lesion. Acupuncture points are selected as shown in Figure 2. Local acupoints: Jianyu (LI 15), Jianliao (TE 14), Jianzhen (SI 9), Binao (LI 14). Distal acupoint: Tiaokou (ST 38). Local non-acupoints (LN): (1) anterior axillary fold; (2) posterior axillary fold; (3) in the shoulder department, 2 cm below Tianzong (SI 11); (4) inside of the upper arm side, Tianfu (LU 3) inward 1 cm, between pericardium meridian and lung meridian. Distal non-acupoint (DN): lateral to the shank, 3 cun below Yanglingquan (GB34), the midway between gall bladder meridian and bladder meridian.

**Figure 2 F2:**
[figure not shown]
The points used in the trial.

We will use sterile, prepacked needles (Huatuo disposable acupuncture needle, Suzhou Medical Co. Ltd., Jiangsu, China). The sizes to be used are 0.25 mm × 40 mm and 0.25 × 75 mm. The doctor will first insert a needle into the distal acupoint or distal non-acupoint (during the needling of these distal points a brief movement of the shoulder is allowed) for 20 minutes, and then insert a needle into the local acupoints or local non-acupoints for a further 20 minutes.

The doctor should ensure the patient is kept in the sitting position, and insert a 0.25 mm × 75 mm acupuncture needle from ST 38 to BL 57 (Chengshan). The needle will be rotated up and down to induce a needle sensation (called ‘de qi’) for 30 seconds. At the same time, the patient will be instructed to demonstrate a small amount of range of motion in the shoulder, such as abduction, external rotation and elevation. Local acupoints will be inserted 10 to 15 mm in depth with a 0.25 mm × 40 mm acupuncture needle. Local non-acupoints and distal non-acupoint will be inserted less than 5 mm in depth with a 0.25 mm × 40 mm acupuncture needle.

### Randomization and blinding

This is a block randomized single blind 2 × 2 factorial design. Randomization is to be conducted by a statistics specialist who will have no contact with the participants. Random numbers with block randomization are generated with SAS software (SAS Institute, Inc., Cary, NC, USA). Participants will be allocated to one of the four groups at a ratio of 1:1:1:1. The research coordinator, who will not be involved with data collection, will inform the acupuncturist of the treatment assignment via the telephone.

The patients, data collection staff, and data analysts will be blinded during the study period. Acupuncturists are not blinded to the treatments they deliver due to the nature of the intervention. During the intervention, the acupuncturist and personnel who collect data will be segregated immediately after the start of treatment and are instructed not to exchange information with each other.

### Primary outcome measures

Shoulder pain intensity will be graded using a 100-mm Visual Analogue Scale (VAS) by patients themselves, with 0 representing ‘no pain at all’ and 100 mm representing ‘the most intense pain imaginable’ [4]. The assessment is at baseline (before treatment initiation), 6 weeks after the first acupuncture, 10 weeks after the first acupuncture and 18 weeks after the first acupuncture.

### Secondary outcome measures

There will be three secondary outcome measures. First, functions of the shoulder joint will be evaluated using the Constant-Murley score (CMS). This consists of four domains: pain (one item), activities of daily living (ADL; three items for activity level, such as work, sports and sleep), one item for hand positioning (rotation), mobility (four items: forward and lateral abduction and elevation, external and internal rotation), and power or strength (one item). Pain and ADL 1 to 3 are interviewed from the patient (self-assessed); all other items are assessed by examiner [8]. The assessment will be performed at baseline (before treatment initiation), 6 weeks after the first acupuncture, 10 weeks after the first acupuncture, and 18 weeks after of the first acupuncture. Second, the quality of life is assessed using Short form-36 (SF-36) [9]. The assessment is at baseline (before treatment initiation), 6 weeks after the first acupuncture, 10 weeks after the first acupuncture and 18 weeks after the first acupuncture. Third, the perceived credibility of acupuncture is evaluated by The Treatment Credibility Scale (TCS) [10] after a 6-week acupuncture session. It is a five-item questionnaire ranging from 1 (not at all) to 5 (very confident). Items are averaged to provide a single treatment credibility score, with high scores reflecting high treatment credibility.

Participants will also be advised to report any adverse events they experience, including discomfort or bruising at the sites of needle insertion, nausea, or feeling faint after a 6-week acupuncture treatment.

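### Treatment credibility is rated only once, after the 6-week course, so a difference between arms could not be separated from perceived benefit

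*Protocol article*

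**What the plan says.** Under Secondary outcome measures, the third outcome is credibility: "the perceived credibility of acupuncture is evaluated by The Treatment Credibility Scale (TCS) [10] after a 6-week acupuncture session". The scale has five items scored 1 to 5, averaged into one score. The same paragraph gives the Constant-Murley score and the SF-36 four time points each (baseline and weeks 6, 10 and 18). The schedule is thus set out scale by scale, and credibility has one rating.

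Under Interventions, after consent and baseline evaluation, "they will receive 12 treatments of acupuncture, one to three times per week for six weeks in total". The TCS therefore follows the whole course.

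Under Primary outcome measures, "Shoulder pain intensity will be graded using a 100-mm Visual Analogue Scale (VAS) by patients themselves", with week 6 as the first assessment after baseline.

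Under Randomization and blinding, "The patients, data collection staff, and data analysts will be blinded during the study period". The consent approach supports this: "Patients are informed in a manner suggesting that four different types of acupuncture treatment are compared some are traditional and others are new", and the words placebo and sham are avoided.

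Real and control needling differ in ways a patient may notice. The needling text under Interventions states "Local acupoints will be inserted 10 to 15 mm in depth" and "Local non-acupoints and distal non-acupoint will be inserted less than 5 mm in depth". At the distal acupoint a 75 mm needle is rotated for 30 seconds to obtain de qi. The distal non-acupoint gets a 40 mm needle.

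**The concern.** The primary outcome is the patient's own pain rating, so it is useful to know whether the four treatments were equally believable to the people doing the rating. Differences in depth at the local points, and in needle length and stimulation at the distal point, give a reason to ask. The TCS is the only stated measure that bears on this.

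A credibility rating made after a full course reflects two things: how convincing the treatment seemed, and how well it appeared to work. If the arms differ in benefit, they can differ in end-of-course credibility even when they were equally convincing at the start. The score is then hardest to interpret when the treatment works. At stake is what the trial can say about equal credibility across arms. The planned factorial analysis of pain is not affected.

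**Working it through.** The protocol gives no TCS mean, standard deviation or expected difference, so there is no plan figure to reproduce. The check has two parts: what a single late score can identify, and an illustration of size.

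**1. What one late score can identify.** Let c be the difference in initial credibility between two arms, Δp the difference in the proportion who respond, and g the extra TCS points that a responder gives because of the benefit. If initial credibility carries through the course,

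week-6 TCS gap = c + Δp × g.

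One observed gap cannot give both terms. With Δp = 0.41, a gap of 0.41 points arises from c = 0 and g = 1.0, and equally from c = 0.41 and g = 0. A gap near zero is compatible with equal initial credibility, but also with an early difference that faded by the end. Hence it is weak reassurance rather than none. A rating taken before benefit is apparent has Δp × g close to zero and estimates c directly.

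**2. Illustration of size, with c = 0 (equal initial credibility).**

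Inputs from the protocol (Sample Size section):
- response rates 65% (verum) and 24% (sham), so Δp = 0.65 − 0.24 = 0.41. Applying these to group A against group D is an assumption; no rates are given for groups B and C;
- 34 evaluable and 41 recruited patients per group, taken as stated.

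Inputs assumed because the protocol gives neither:
- g = 0.25, 0.5, 1.0 or 1.5 points;
- TCS standard deviation (SD) among patients of the same response status = 0.6, 0.8 or 1.0.

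Formulas:
- gap = 0.41 × g;
- s = √(SD² + g² × (0.65 × 0.35 + 0.24 × 0.76)/2) = √(SD² + 0.205 g²);
- chance of a significant gap favouring group A at two-sided 0.05 = Φ(gap / (s × √(2/n)) − 1.96).

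Worked case, g = 1.0, SD = 0.8, n = 34: gap = 0.41; s = √(0.64 + 0.205) = 0.919; standard error = 0.919 × √(2/34) = 0.223; 0.41/0.223 = 1.84; Φ(1.84 − 1.96) = 45%.

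Chance of a significant gap, n = 34 / n = 41 per group:

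| g | gap | SD 0.6 | SD 0.8 | SD 1.0 |
|---|---|---|---|---|
| 0.25 | 0.10 | 10% / 12% | 8% / 8% | 6% / 7% |
| 0.5 | 0.21 | 26% / 30% | 17% / 20% | 13% / 15% |
| 1.0 | 0.41 | 61% / 70% | 45% / 52% | 34% / 39% |
| 1.5 | 0.62 | 80% / 87% | 68% / 76% | 56% / 63% |

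With no gap, the reference value in this one direction is 2.5% (5% over both directions). The range is wide because g and the SD are unknown. The table shows the mechanism and does not measure its size in this trial.

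**The case against.** The strongest reply is that the protocol lists the TCS simply as a secondary outcome on perceived credibility, and an end-of-course score is a legitimate summary of all 12 sessions. An early score would miss credibility lost later. This stands, and is why the 6-week score should stay. It does not remove the difficulty of reading a difference between arms at week 6.

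The trial also has other protection against expectation effects: randomization, needling at both local and distal sites in every arm, neutral consent wording, and data collectors kept apart from the acupuncturists. These stand too.

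Several stronger readings are tempting, and the document does not support them.
- A reader might infer that the TCS is the trial's blinding test and fails as one. The protocol never gives it that role, and credibility is not a guess at allocation. An early TCS would not test blinding either.
- A reader might worry that adjusting for the week-6 TCS would remove a true effect. The Data analysis section names two fixed factors and their interaction, with no TCS covariate.
- A reader might conclude that every pain contrast depends on this score. The TCS enters no stated primary analysis.
- A reader might assume the TCS and the week-6 pain rating are taken at one visit, or that all real needling involves de qi. The first is not stated, and de qi is stated only for the distal acupoint.

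On cost, the first sessions are not stated assessment points and are delivered by unblinded acupuncturists, so collection would have to be arranged.

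**Conclusion.** The point holds as a limit on interpretation. The article itself fixes a single credibility rating after the full course. A between-arm difference at that time could reflect lower initial credibility of control needling, a rise in the score due to benefit, or both, and the score alone cannot separate them. Similar scores would give some reassurance, but weak.

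The size cannot be computed from the document. Under the assumptions shown, with uplifts of 0.5 to 1.0 points, the gap created by benefit alone would be 0.21 to 0.41 points and would be significant 13% to 70% of the time. The conclusion rests on benefit having some influence on rated credibility (g above zero) and on the arms differing in benefit. If either fails, the late score is not distorted in this way.

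This is an inexpensive improvement to what the trial can say about equal credibility. It is neither a contradiction in the protocol nor an error in the primary analysis.

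**What to change.** Add the same five-item TCS after the first or second treatment session, before benefit can reasonably be judged. Have patients complete it themselves, or have blinded staff collect it, and not the acupuncturist. Name this early score as the one used to compare credibility between the four arms, and keep the 6-week TCS as a descriptive outcome.

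The cost is one short form outside the stated assessment time points, with some arrangement to keep it away from the unblinded acupuncturist. The Trial status section says recruitment is under way, so patients already past their early sessions will have no early score. The comparison should be reported for those who do, with their number by arm. Sample size, treatment and the primary analysis do not change.

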### Sample Size

According to the previous pilot study [4],an average 20-point reduction on the VAS scores relating to shoulder pain has a clinically significant difference, and percentages of responders for the primary endpoint are verum 65%, sham 24%. The following formula is used for a four-group trial [11]:

$$n=\frac{2\lambda }{{\left(2\mathrm{si}n^{‒1}\sqrt{P_{\text{max}}}‒2\mathrm{si}n^{‒1}P_{\text{min}}\right)}^{2}}$$

Based on 0.9 power to detect a significant difference (α = 0.05,ν = 4-1 = 3,λ =14.17), the required sample size is 34 patients in each group. Allowing for 20% attrition, we should recruit 164 patients, with 41 in each group.

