### Data analysis

Statisticians who are independent from the research team will analyze data in accordance with a 2 × 2 randomized factorial study design. Every analysis is to be conducted using the software of SPSS 12.0. The statistical model includes two fixed factors (local acupoints and distal acupoints). Interaction is to be evaluated by the interaction term in the analysis of variance (ANOVA) model and visual assessment of profile plots.

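### The stated 0.9 power belongs to a four-group test of responder percentages that is not planned, so power for the 2×2 ANOVA on VAS and for A vs B and A vs C is unstated

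*Protocol article*

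**What the plan says.** The Sample Size section of the protocol article mentions a VAS benchmark: "an average 20-point reduction on the VAS scores relating to shoulder pain has a clinically significant difference". It then turns to responders, stating that "percentages of responders for the primary endpoint are verum 65%, sham 24"%. "The following formula is used for a four-group trial": an arcsine formula in the largest and smallest response rates, with "α = 0.05,ν = 4-1 = 3,λ =14.17". "Based on 0.9 power to detect a significant difference", it arrives at 34 per group, raised to 41 per group and 164 in total for 20% attrition.

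The other sections describe a different endpoint and test:

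- Primary outcome measures: "Shoulder pain intensity will be graded using a 100-mm Visual Analogue Scale (VAS) by patients themselves". No responder is defined there or elsewhere.
- Data analysis: "The statistical model includes two fixed factors (local acupoints and distal acupoints"), with an interaction term in the ANOVA.
- Background: the purpose is to learn whether the combination is "more effective than local acupoints or distal acupoints alone". The Discussion repeats this. In terms of the four groups, that is A vs B and A vs C.

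**The concern.** The sample size is computed for one test and the trial plans others. The calculation concerns a binary response and a global test across four groups (3 df). The analysis concerns a continuous score and three effects of 1 df each: two main effects and an interaction. The question posed is a pair of simple contrasts. The gap that drives the calculation, 65% against 24%, is verum against sham, which in this design is A vs D. Neither A vs B nor A vs C has that gap unless the single-component group responds no better than sham.

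The stated 0.9 is therefore not a property of the planned analysis. A reader who meets a non-significant A−B, A−C or interaction has only this figure by which to judge how informative the result is, and it does not describe those tests.

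**Working it through.** **1. The plan's own figure.** Inputs from the Sample Size section: Pmax = 0.65, Pmin = 0.24, α = 0.05, 3 df, λ = 14.17, power 0.9.

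- The non-centrality of a chi-square test with 3 df, α = 0.05 and power 0.9 is 14.171. So λ is right, and it belongs to a global four-group test.
- With a root on both terms: 2·asin√0.65 − 2·asin√0.24 = 1.8755 − 1.0239 = 0.8515. Then n = 2 × 14.17 / 0.8515² = 28.34 / 0.7251 = 39.1, so 40 per group.
- As displayed, with no root on Pmin: the difference is 1.3908 and n = 14.7, so 15. The missing root may be a typesetting slip.
- With no root on either term: the difference is 0.9304 and n = 32.7, so 33.
- None of these gives 34. At 34 per group, λ = 34 × 0.7251 / 2 = 12.33 and the 3-df power is 0.85.

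The 20-point VAS figure appears in none of these steps.

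**2. Power of the planned VAS tests.** Evaluable per group: 41 × 0.8 = 32.8, taken as 33; error df = 4 × 33 − 4 = 128. The article gives no SD and no between-group VAS difference. I assume a residual SD of 25 mm (range 20 to 30) and show true effects of 10 and 20 mm. Power is from the non-central t, two-sided 0.05, without multiplicity adjustment.

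Standard errors for SD s and n = 33:

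- main effect: s√(1/n) = 25 × 0.1741 = 4.35 mm
- A−B or A−C: s√(2/n) = 25 × 0.2462 = 6.15 mm
- interaction contrast A−B−C+D: s√(4/n) = 25 × 0.3482 = 8.70 mm

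| Test | True 10 mm: SD 25 (SD 20 to 30) | True 20 mm: SD 25 (SD 20 to 30) |
|---|---|---|
| Main effect | 0.63 (0.81 to 0.48) | >0.99 (>0.99 to 0.97) |
| A−B or A−C | 0.36 (0.52 to 0.27) | 0.90 (0.98 to 0.77) |
| Interaction | 0.21 (0.30 to 0.16) | 0.63 (0.81 to 0.48) |

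The difference detectable with power 0.9 is about (1.96 + 1.28) × SE. At SD 25 that is 14 mm for a main effect, 20 mm for A−B and 28 mm for the interaction.

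**3. How the effects are linked.** The two main effects are [(A+B) − (C+D)]/2 and [(A+C) − (B+D)]/2. Their sum is A − D, with or without interaction. If A−D is 20 mm, they average 10 mm; two main effects of 20 mm each need A−D of 40 mm.

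**4. The same on responders.** A vs B on the arcsine scale with 33 per group, A = 65%:

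- B = 24% (equal to sham): z = 0.8515/√(2/33) = 3.46, power 0.93.
- B = 44.5% (midway, an assumption): the arcsine difference is 0.4149, z = 1.69, power 0.39 (about 0.40 with 34 per group).

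**The case against.** A reader might infer that power for the planned tests is far below 0.9. The article does not establish that. It says only that a 20-point reduction matters clinically; it does not assign that figure to A−D, to a main effect or to A−B. If 20 mm is the true main effect, power is 0.97 or more for SDs up to 30 mm, and a true A−B of 20 mm has 0.90 at SD 25. The responder gap may also stand for a larger effect than 20 mm. On a normal scale with common variance, 65% against 24% is 0.385 + 0.706 = 1.09 SD. Half of that as a main effect has power of about 0.88, and as A−B about 0.60.

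A reader might also infer that A−B and A−C must be smaller than the verum-sham gap. They need not be. If the components work only together (B = C = D), both equal the full gap. The Discussion expects local points to relieve pain and distal points to improve motion, so on VAS pain C may lie close to D, and A−C close to the full gap. An even split of the effect is one scenario among several, and it implies zero interaction, so it cannot be combined with a 10 mm interaction. Nor does the article say that A must beat both B and C significantly, or how a null result would be read.

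These points limit what can be said about size. They leave the mismatch untouched: no choice of SD or effect split makes a 3-df test of proportions the planned analysis. Two of them also cut the other way. The Discussion's expectation that local points relieve pain implies that B is better than D, so A−B falls short of A−D. And under pure synergy with A−D = 20 mm and SD 25, each main effect is 10 mm and the interaction 20 mm, and each has power of only 0.63.

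**Conclusion.** The point holds as a mismatch, and that part needs no assumption. The 0.9 is computed for a test and an endpoint that the outcome and analysis sections do not use, so it applies neither to the 2×2 ANOVA on VAS nor to A vs B and A vs C. It is also wrong for its own test: 40 per group are needed, and 34 give about 0.85.

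Power for the planned tests is unstated. It may be near or above 0.9 for main effects or for A−B if the true difference is 20 mm. It is well below 0.9 for 10 mm differences and, over the assumed SDs, for an interaction of up to 20 mm. These figures rest on 33 evaluable per group, an assumed SD of 20 to 30 mm and the effects shown. A−B and A−C are smaller than the verum-sham gap unless the single components do nothing alone. A general claim that power is far lower than 0.9 would go beyond what the article supports.

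**What to change.** Keep N = 164 and rewrite the Sample Size section:

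- State that the 3-df responder calculation does not give the power of the primary analysis, and withdraw the 0.9 in that role.
- If the calculation is kept as history, correct it: root on both terms, 40 per group for 0.9, about 0.85 with 34.
- For 164 randomised and about 33 evaluable per group, give the power or the detectable difference on VAS for each main effect, the interaction, A−B and A−C. Name the SD and the effects assumed, with their source, and show a range.

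This is a change of wording: no extra patients, and no change to design or analysis. The cost is a less favourable stated power, most of all for the interaction and the A−B and A−C contrasts.

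### The stated 34 patients per group does not follow from the protocol's own formula and inputs, which give 40; at 34 the power on the same criterion is about 85%, not 90%.

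*Protocol article*

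**What the plan says.** The Sample Size section of the protocol article prints a complete calculation.

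- **Planning rates:** "percentages of responders for the primary endpoint are verum 65%, sham 24" (per cent), taken from a pilot study.
- **Method:** "The following formula is used for a four-group trial", followed by an arcsine expression in Pmax and Pmin. As it appears in the text, the square root covers Pmax but not Pmin.
- **Error rates and noncentrality:** "Based on 0.9 power to detect a significant difference", with "α = 0.05,ν = 4-1 = 3,λ =14.17".
- **Result:** "the required sample size is 34 patients in each group".
- **Recruitment:** "Allowing for 20% attrition, we should recruit 164 patients, with 41 in each group".

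Allocation is equal across the four groups (Randomization and blinding).

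**The concern.** Formula, inputs and answer are all on the page, so the answer can be checked without any outside assumption, and it does not come out. This is not detail left to a fuller document: the printed pieces disagree with each other.

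This is the only sample size justification in the article, and the target of 164 is built on the 34. If 34 is too small for the stated inputs, the 90% is too high. A reader who relies on it to interpret a non-significant result on this criterion would put the risk of missing the planned difference at 10%, when the protocol's own inputs imply about 15%.

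**Working it through.** **Inputs** (all from the Sample Size section): Pmax = 0.65, Pmin = 0.24, α = 0.05, ν = 3, λ = 14.17, power 0.90, 20% attrition, 41 recruited per group.

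**Step 1: is λ right?** The noncentral chi-square with 3 df, tested at α = 0.05, needs a noncentrality of 14.171 for 90% power. The printed 14.17 is correct, so the fault lies further on.

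**Step 2: try to reproduce 34.** The formula is n = 2λ / h², with 2λ = 28.34.

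| Reading | h | h² | n | Per group |
|---|---|---|---|---|
| Root on both: 2·asin√0.65 − 2·asin√0.24 | 1.8755 − 1.0239 = 0.8515 | 0.7251 | 28.34 / 0.7251 = 39.08 | 40 |
| As printed: 2·asin√0.65 − 2·asin(0.24) | 1.8755 − 0.4847 = 1.3908 | 1.934 | 28.34 / 1.934 = 14.65 | 15 |
| Stated | – | – | – | 34 |

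Neither reading returns 34. Against 40, the stated figure is 6 patients per group short (6/40 = 15%).

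**Step 3: look for an innocent explanation.**

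- Rounded rates: taking 64.5–65.5% against 23.5–24.5%, n runs from 37.1 to 41.2.
- Degrees instead of radians, properly converted: 39.1 again.
- λ for 2 df (12.65): 2 × 12.65 / 0.7251 = 34.9, so 35, and this contradicts the printed ν and λ.
- λ for 85% power at 3 df (12.30): 2 × 12.30 / 0.7251 = 33.9, so 34. This contradicts the stated 90% and the printed λ.
- A two-group, two-sided comparison of proportions at 90% power with continuity correction: 34 (29 without the correction). This is not the four-group formula that the section says was used.
- Other rates with the printed λ: 68% v 24% gives 33.8, and 65% v 21% gives 33.2. Neither pair is stated.

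Some of these routes reach 34, but each requires a printed input or the printed method to be wrong.

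**Step 4: power on the protocol's own criterion.** The noncentrality is n·h²/2, and power is the upper tail of the noncentral chi-square with 3 df beyond the 5% critical value of 7.815.

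| Evaluable per group | Noncentrality | Power |
|---|---|---|
| 32.8 (41 × 0.8) | 11.89 | 83.7% |
| 34 | 12.33 | 85.1% |
| 39 | 14.14 | 89.9% |
| 40 | 14.50 | 90.7% |
| 41 (no attrition) | 14.87 | 91.4% |

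**The case against.** The arithmetic is not in dispute. The case on the other side concerns what follows from it.

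1. **The 85% is a minimum.** The formula uses only the highest and lowest rates and assumes the least favourable position for the two middle groups, halfway between on the arcsine scale. At 34 per group, with the same 65% and 24%, the 3-df test has about 96% power if three groups share one rate (noncentrality 0.75 × 34 × 0.7251 = 18.5) and about 99% if two groups lie at each rate (34 × 0.7251 = 24.7). This stands as a caveat. It applies equally to the stated 90%, so 90% against 85% is a like-for-like comparison.
2. **The criterion is not the planned analysis.** The primary outcome is VAS pain intensity, and Data analysis describes a 2 × 2 factorial ANOVA. No SD is given, so power for that model cannot be computed here. This also stands: neither 90% nor 85% describes the ANOVA, and the error alone does not show how a null ANOVA result would be read. It does not make 34 correct.
3. **The missing root may be a typesetting or conversion slip.** It may well be. The finding does not need it, because 34 is wrong with or without the root.
4. **The loss is modest and the cause unknown.** It is about 5 to 6 points of power, and 41 per group would exceed the 40 needed if almost nobody dropped out. Since other calculations reach 34, a misreported input or method is possible. The authors should therefore be asked what was done before a replacement figure is settled.

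**Conclusion.** The concern holds. The stated inputs require 40 evaluable patients per group, not 34. On the protocol's four-group responder criterion, 34 per group gives about 85% power, and about 84% if 20% of the 41 recruited are lost. The chance of missing the planned difference is then about 15–16% rather than 10%.

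This rests on the printed rates, α, ν and λ, and on the arcsine formula with the root on both proportions; the literal printed form does not give 34 either. The power figures are minimum values over the positions of the two middle groups and say nothing about the factorial ANOVA. The loss of power is moderate. The reason to correct it is that the trial's only sample size justification cannot be reproduced and claims more power than its own inputs support.

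**What to change.** First establish which calculation produced 34, and print the rates, λ or method actually used if they differ from those shown.

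If the printed inputs stand:

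- put the square root on Pmin in the formula, if it is missing in the published version;
- give the result as 39.1, so 40 evaluable per group for 90% power;
- keep 164 and restate the power as about 85% with 34 evaluable per group, or about 84% with 20% of 41 lost;
- say that this is minimum power for the four-group responder comparison, not for the factorial ANOVA.

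The cost is a wording correction in one section. No patients are added and nothing in the conduct of the trial changes; the stated power becomes less favourable. Holding 90% after attrition would be a different decision: 40 / 0.8 = 50 per group, or 200 in total.
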